#### 6.4.4 The “Follow-up Questionnaire”

The “Follow-up Questionnaire” is a study-specific, non-validated instrument and is developed by WHC to provide measures that will reflect patient perception and satisfaction of bowel management, including TAI therapy and the use of Navina Smart system.

The Navina-specific questions relates to 5 dimensions; *Preparation, Activation, Instillation, Evacuation and Disassembling and Cleaning*. Additionally, the questionnaire contains questions to address product compliance and frequency of UTI.

The “Follow-up-Questionnaire” is self-administrated and will be given to all subjects at 3-months follow-up (Visit 2) and at 12- months follow-up (Visit 3) or at end of the treatment period for those subjects with early withdrawal from the study. The subject will be provided with personal log-in details to *ViedocMe*, the patient interface of the eCRF, which will be used to complete the “Follow-up Questionnaire”. If, at any time during the study and for any reason, the subject is unable to complete web-based questionnaires, the subject will be provided a paper questionnaire. Study site personnel will then enter the data into the study data base.

Applicable scores and results from the questionnaire will be analysed and presented using descriptive statistics. Quantifiable data on healthcare utilization will be used in health economic analyses to assess changes in costs related to treatment with Navina Smart system.

## 7 STATISTICAL CONSIDERATIONS

### 7.1 Statistical Evaluation – General Aspects

Epidemiological methods will be used for the analysis of study data being a result of a non-interventional study design. Descriptive statistics, i.e. number of subjects, mean, median, standard deviation, minimum and maximum values for continuous data and frequencies and percentages for categorical data will be used as applicable. P-values below 5% will be considered statistically significant even though it is recognized that multiple hypotheses will be tested.

#### 7.1.1 Demographics and Other Baseline Characteristics

Baseline data as well as other covariates will be presented by means of descriptive statistics and investigated by using epidemiological methods.

#### 7.1.2 Covariates and Prognostic Variables

No considerations to potential covariates and/or prognostic factors are taken in the study design. Potential influence on any covariates and/or prognostic variables to the outcome of the study will be investigated in the statistical analysis using epidemiological methods.

#### 7.1.3 Handling of Dropouts and Missing Data

Subjects dropping out will be compensated for in the sample size estimation. In case of higher drop-out than accounted for, it is recognized that recruitment may be extended to involve at least the minimum number of evaluable subjects since no risks for the subjects can be identified (i.e.

prescribed treatment are being observed). This is to ensure a representative sample for the purpose of the study/epidemiologic survey. Missing data will not be imputed.

#### 7.1.4 Multi-Centre

This study is a multi-centre study. However, there is no a priori reason to suspect that there will be any qualitative differences between the study sites regarding any of the outcome variables in the study. Therefore, primary statistical analysis will not include centre in the model but subgroup analyses and health economic evaluations may use and present result by centre as applicable.

### 7.2 Description of Analysis Sets

The study will be analysed using a Per Protocol (PP) and an Intention To Treat (ITT) approach. Subjects fulfilling the inclusion criteria but none of the exclusion criteria and have been treated according to the protocol without any major deviations will be included in the PP analysis set. All correctly included patients will be included in the ITT analysis set. All treated subjects will be included in the safety analysis set. Treatment efficacy related conclusions will be based on the results from the PP analysis and confirmed by an analysis of the ITT analysis set (only for the primary objective) and demography and treatment safety related conclusions will be based on the results from the safety analysis set.

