## 4.5.2 Procedures for Discontinuation

Subjects not meeting the inclusion/exclusion criteria for this study should, under no circumstances, be enrolled into the study. If subjects not meeting the study criteria are enrolled in error, or where subjects subsequently meet the criteria for discontinuation (see Section 4.5.1) after enrolment, they must be discontinued from study participation/treatment immediately. When applicable, subjects who discontinue prematurely, for any reason, should always be asked about the reason(s) for their discontinuation, the presence of any AE, completion of applicable sections of the eCRF and relevant PROs.

To the furthest extent possible, subjects who discontinue should be seen and assessed by an investigator for follow-up of AE and return of study devices and other study materials.

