## 6.4 Patient-Reported Outcomes (PROs)

### 6.4.1 The Neurogenic Bowel Dysfunction score

To evaluate the effect of Navina System, a patient friendly version of the validated standardized NBD score  questionnaire will be used. The NBD score is a symptom-based score for neurogenic bowel dysfunction that takes into account both constipation and faecal incontinence, and weighs each symptom of NBD according to its impact on QoL in persons with spinal cord injury. The NBD score has a 10-item symptom severity scale to measure the parameters, faecal incontinence, constipation and obstructed defecation.

Each item is assigned a score based on odds ratios for associations between items and impact on QoL. Negative changes in NBD score correspond to an improvement in bowel-related symptoms, and the total NBD score can range from 0 (very minor bowel dysfunction) to 47 (severe bowel dysfunction).

The NBD score is self-administrated and will be completed by all subjects at baseline (visit 1), at 3 months follow-up (visit 2), in connection to the 6 and 9 months telephone follow-ups and at 12 months follow-up (Visit 3) or at end of the treatment period for those subjects with early withdrawal from the study. The subject will be provided with personal log-in details to *Viedoc™Me*, the patient interface of the eCRF, which will be used to complete the NBD score at baseline. The NBD score at 3, 6, 9 and 12 months follow-up will be completed using the Navina Smart app (see further instructions in 5.1.2). If, at any time during the study and for any reason,

the subject is unable to complete web-based questionnaires, the subject will be provided a paper questionnaire. Study site personnel will then enter the data into the study data base.

Applicable scores and results from the questionnaire will be analysed and presented according to the user instructions from the provider. The results from the NBD score at baseline and at the 3, 6, 9 and 12 months follow-up will be compared.

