### 7.4 Determination of Sample Size

This study aims to look at change in NBD score (range from 0 (very minor bowel dysfunction) to 47 (severe bowel dysfunction)) after introducing TAI with the Navina Smart system in a population with a common feature of having neurological bowel dysfunction. Each patient serves as his/her own control, by measuring change in NBD score before and after treatment with the Navina Smart system. The NBD score is a validated questionnaire and tool that correlates neurological bowel dysfunction to QoL. In this study a patient friendly version of the NBD Score will be used.

To determine the sample size of the study the following formula is used, referred to in Lachin 1981, considering the fact that a pair wise comparison is made.

$$N = \frac{(Z_{\alpha} + Z_{\beta})^2 \sigma^2}{\mu_1^2}$$

Where:

$\mu_1$  = minimal important difference or difference worth detecting

N = Total number of patients

$Z_{\alpha} = 1.96$  (5% two-sided significance level)

$Z_{\beta} = 1.28$  ( $1-\beta = 0.90$ ), 90% power or 0.84 ( $1-\beta = 0.80$ ), 80% power

$\sigma$  = standard deviation of difference in NBD score between baseline (without Navina™) and 3 months use of Navina™.

The table below shows number of patients needed using different levels of minimal important difference and standard deviations, using 90% power and 5% two-sided significance level.

Total sample size for paired observations where  $\sigma$  is known and defined as standard deviation of difference between baseline and follow-up.

| $\mu 1$    | $\sigma = 2.0$ | $\sigma = 2.1$ | $\sigma = 2.2$ | $\sigma = 2.5$ |
|------------|----------------|----------------|----------------|----------------|
| 0.8 | 66             | 73             | 80             | 103            |
| 1.0 | 43             | 47             | 51             | 66             |
| 1.2 | 30             | 33             | 36             | 46             |
| 1.5 | 19             | 21             | 23             | 30             |
| 2.0 | 11             | 12             | 13             | 17             |
| 2.5 | 7              | 8              | 9              | 11             |

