The chosen minimal important difference for the study is related to the fact that also small difference could be clinically meaningful for the patients. In addition, depending on baseline NBD score level, smaller, but still valid, changes may be present when starting at a level closer to the inclusion cut of 10 than if the starting point is around 14. For this reason we believe a minimal important difference level valuable to detect in the study of ~0.8 would be representative.

Christensen et al describe in their sample published in 2008 a mean difference in NBD score of -4.5 with corresponding 95% confidence interval of -6.6 to -2.4 after introducing TAI for a 10 weeks' period. This indicates that the expected standard deviation for the difference between baseline and follow up in NBD score would lie somewhere around 2.1-2.2. For detection of a minimal important difference of 0.8, with an expected standard deviation of 2.2, a total of 80 (90% power) subjects who has been using Navina Smart for 3 months are required. However, since higher variability than expected and high drop-out rates may risk the final numbers additional patients must be accounted for. For example, Gosselink et al. reported a discontinuation rate of 55% when introducing TAI therapy in their sample reported in 2004 and Christensen et al. observed a discontinuation rate of 45%, why it is recommended to recruit at least 150 patients in the current study. This will allow 70 of 150 (47%) to drop-out from the study with maintained 90% power to detect a difference of 0.8 between a baseline NBD score (without Navina Smart) and after using Navina Smart for 3 months.

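### Efficacy is concluded from the per-protocol set without imputation while the sample size tolerates 47% drop-out, and the ITT analysis as written is no check on that drop-out

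*Protocol*

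**What the plan says.** Section 7.2 defines the per-protocol (PP) set as eligible subjects treated according to the protocol without major deviations, and the ITT set as all correctly included patients. It then states: "Treatment efficacy related conclusions will be based on the results from the PP analysis and confirmed by an analysis of the ITT analysis set", the latter for the primary objective only. Section 7.1.3 states "Missing data will not be imputed". If drop-out is higher than planned, it allows recruitment to be extended until there are enough evaluable subjects, and explains: "This is to ensure a representative sample for the purpose of the study/epidemiologic survey".

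Table 6 places the primary outcome at Visit 1 and Visit 2, and section 7.3 tests it with the Wilcoxon signed rank test. Section 7.4 reads: "For detection of a minimal important difference of 0.8, with an expected standard deviation of 2.2, a total of 80 (90% power) subjects". It limits these 80 to "subjects who has been using Navina Smart for 3 months are required". It recruits 150 so that 70 may drop out, and cites discontinuation rates of 55% and 45% from earlier irrigation studies.

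For subjects who leave, section 4.5.1 says that data handling is described in section 7.2. Section 4.5.2 says that subjects enrolled in error, or who meet a discontinuation criterion, must stop: "they must be discontinued from study participation/treatment immediately". It also asks for relevant patient-reported outcomes at that point. Section 6.4.1 has the NBD score completed at the scheduled times "or at end of the treatment period for those subjects with early withdrawal from the study".

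**The concern.** Subjects who stay on irrigation for 3 months are likely to be those whom it helps. An estimate confined to them describes persisters, not everyone who starts the device. Section 3.3 attributes any change in NBD score to the device and concludes that no control group is needed. There is therefore no comparator in which the same selection could cancel, and the bias runs in the device's favour. Section 1.1 says the study is meant to assure professionals and users that the product is effective, which is a statement about those who start.

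An ITT analysis would normally guard against this. Here it meets the same obstacle: a paired test without imputation cannot use a subject who lacks the second score. Adding subjects until enough are evaluable restores the number of completers. It does not make them representative of those enrolled.

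**Working it through.** **Plan's own figures.** Inputs from section 7.4: Z values 1.96 and 1.28, "using 90% power and 5% two-sided significance level", difference 0.8, SD of the paired difference 2.2. The SD is taken as given here.

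- N = (1.96 + 1.28)² × 2.2² / 0.8² = 10.4976 × 4.84 / 0.64 = 79.4, so 80. This agrees with the protocol.
- 80 / (1 − 70/150) = 150, and 70/150 = 46.7%. This agrees too.
- The 90% power therefore refers to an effect of 0.8 among 80 subjects with 3 months of use.

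**Who enters each analysis.**

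| Subject | PP | ITT as written |
|---|---|---|
| Completes 3 months, no major deviation | yes | yes |
| Major deviation, has Visit 2 score | no | yes |
| Stopped device, has Visit 2 score | presumably no | yes |
| No 3-month score, early-withdrawal score only | no | no stated role |
| No score after baseline | no | no |

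The two sets differ in the second and third rows. Drop-out without a 3-month score falls in the last two, where ITT adds nothing.

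**Dilution.** Assume that all 70 leave before month 3 and have mean change 0.

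- Completer effect 0.8: 0.8 × 80/150 = 0.43 over all enrolled. At 45% drop-out it is 0.8 × 0.55 = 0.44, and at 55% it is 0.8 × 0.45 = 0.36.
- Completer mean −4.5 (the published mean change cited in section 7.4, used only as an example): −4.5 × 80/150 = −2.4.
- Completers would need 0.8 × 150/80 = 1.5 points for the mean over all enrolled to reach 0.8.
- A mean worsening of 0.8 × 80/70 = 0.91 points in the 70 would cancel a completer effect of 0.8.

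**False-positive rate.** Assume a true mean change of zero over all enrolled, 80 of 150 retained, and staying and improvement jointly normal with correlation ρ. The ρ values are assumptions; the documents give none.

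- Retained proportion p = 80/150 = 0.533, selection threshold c = −0.084, λ = φ(c)/p = 0.745.
- Mean improvement among completers = ρ × 0.745 SD. Their SD is reduced by the factor √(1 − ρ² × 0.618), where 0.618 = λ(λ − c).
- Non-centrality = ρ × 0.745 × √80 / √(1 − ρ² × 0.618).

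| ρ | Completer shift (SD units) | Non-centrality | Rejects in the device's favour |
|---|---|---|---|
| 0 | 0 | 0 | 2.5% |
| 0.1 | 0.075 | 0.67 | 10% |
| 0.2 | 0.149 | 1.35 | 27% |
| 0.3 | 0.224 | 2.06 | 54% |

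These rates do not depend on the SD. A simulation with the Wilcoxon test itself (4,000 runs per value) gave 2.4%, 9%, 26% and 51%. At the protocol's SD of 2.2, the shift for ρ = 0.3 is 0.224 × 2.2 = 0.49 points, against a minimal important difference of 0.8.

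**The case against.** Four objections have force.

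First, 47% is an allowance. A reader might infer that the protocol expects this loss, or treats it as a ceiling. It does neither: the margin also covers higher variability, the cited rates lie on both sides of it, and section 7.4 does not say when those discontinuations occurred. Drop-outs after month 3 keep their primary score. The dilution figures are thus an illustration at the allowance.

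Second, a reader might infer that ITT omits exactly the subjects that PP omits, or that most who stop the device have no 3-month score. The documents do not support that. The Follow-up Questionnaire at 3 months asks whether the subject still performs irrigation, which presupposes that some who stopped are still in the study. Stopping the device is not itself a listed discontinuation criterion. The wording in 4.5.2 that runs participation and treatment together is ambiguous, but it does not settle the matter.

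Third, the size of the bias is assumed. No correlation between staying and improving is given, and the diluted −2.4 is still three times 0.8, so that example does not reverse the conclusion.

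Fourth, an SAP that is not shown might define the use of the early-withdrawal score. That may be so. But the protocol itself chooses PP as the lead, forbids imputation, and sends the reader to a rule that is not there.

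**Conclusion.** The concern holds in this form. Followed as written, the plan bases its efficacy conclusion on subjects who persisted, in a single-arm study that credits all change to the device. The ITT analysis is limited to subjects with a 3-month score and so does not check the effect of drop-out. The pointer from 4.5.1 to 7.2 leads to no rule, and the NBD score collected at early withdrawal has no stated role.

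At the protocol's own allowance, a completer effect of 0.8 is about half that (0.43) over all enrolled if the 70 leave before month 3 and do not change. With a true mean change of zero, a modest assumed correlation of 0.2 or 0.3 raises the chance of a result in the device's favour from 2.5% to about 27% or 54%. That the analysis is selective follows from the text. How large the bias is depends on these assumptions.

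**What to change.** - **Section 7.2:** make all correctly included subjects the primary set and PP supportive. State how discontinued subjects are handled, so that the reference in 4.5.1 leads somewhere.
- **Section 4.5.2:** separate stopping the device from leaving the study for data collection. Subjects who stop but do not withdraw consent still complete the 3-month NBD score by the existing web or paper route.
- **Section 7.1.3:** for the primary endpoint, replace the ban on imputation with a rule that uses the early-withdrawal NBD score where no 3-month score exists. Add sensitivity analyses that assume no change, and worsening, in the remaining non-completers.
- **Section 7.3:** for these analyses, name an estimator or a signed-rank variant that retains zeros. The usual Wilcoxon test discards them, so assigning no change would simply return the result without those subjects.
- **Section 7.1.3:** delete the sentence claiming a representative sample, and report the proportion discontinued by month 3 beside the primary result.

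The cost is protocol wording, some extra follow-up and a little more analysis. The reported mean change is likely to be smaller. Power over all enrolled may also fall. By normal approximation with 150 enrolled, 70 non-completers of mean change 0 and a completer effect of 0.8, it is 88% if each of the 70 has exactly zero change and 65% if their SD is 2.2.

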**Table 1 Secondary Objectives**

| Secondary Objective                                                                                                             | Secondary Outcome Variable                                           |
|---------------------------------------------------------------------------------------------------------------------------------|----------------------------------------------------------------------|
| To investigate the change of QoL status in the selected patient population (absolute values)                                    | EQ-5D-3L variables                                                   |
| To investigate NBD symptoms after 6, 9 and 12 months use of Navina Smart system                                                 | NBD score                                                            |
| To investigate study product compliance                                                                                         | PRO variables (“Do you still perform TAI with Navina Smart?” Yes/No) |
| To investigate patient perception and satisfaction of bowel management including TAI therapy and use of the Navina Smart system | PRO variables                                                        |
| To investigate frequency of UTI                                                                                                 | PRO variables                                                        |
| To perform health economic analyses using QoL data and PRO variables                                                            | EQ-5D
PRO variables                                               |

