## 4.5 Discontinuation of Study Participation

### 4.5.1 Criteria for Discontinuation

Subjects may be discontinued from study participation/treatment at any time. Specific reasons for discontinuing a subject from this study are:

- Voluntary discontinuation by the subject who is at any time free to discontinue his/her participation in the study, without prejudice to further treatment.
- Safety reasons as judged by the investigator and/or WHC.
- Severe non-compliance to protocol as judged by the investigator and/or WHC.
- Incorrect enrolment i.e., the subject does not meet the required inclusion/exclusion criteria for the study.
- Subject lost to follow-up.

Handling of data for discontinued subjects is described in **Section 7.2**.

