**Table 6 Outcome Variables**

| Objective                                                                                                                  | Outcome Variable                                                           | Method                                                                                                                                                                                                             |
|----------------------------------------------------------------------------------------------------------------------------|----------------------------------------------------------------------------|--------------------------------------------------------------------------------------------------------------------------------------------------------------------------------------------------------------------|
| To investigate the change of QoL status in the selected patient population.                                                | EQ-5D-3L.                                                                  | Analyses of absolute values and change between measurements according to instructions from the provider (EuroQoL Group)  of EQ-5D-3L at baseline, 3 months and 12-months.
See section 6.4.2 |
| To investigate study product compliance.                                                                                   | PRO variables (“Do you still perform TAI with the Navina System?” Yes/No). | Descriptive analysis of data collected from patient questionnaires at 3 and 12 months.
See section 6.4.4                                                                                                 |
| To investigate NBD symptoms after 6, 9 and 12 months use of Navina™ System.                                                | NBD Score.                                                                 | Analyses of absolute values and change between measurements according to instructions from the provider of the validated NBD Score  at Baseline, 3, 6, 9 and 12 months.
See section 6.4.1   |

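### Section 7.2 confines the ITT analysis to the primary objective, so later NBD scores rest on the per-protocol set alone, and no set is named for compliance and satisfaction

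*Protocol*

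**What the plan says.** Section 7.2 defines three sets and gives each a use.

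- **PP:** eligible subjects who "have been treated according to the protocol without any major deviations will be included in the PP analysis set". What counts as a major deviation is not defined. "Treatment efficacy related conclusions will be based on the results from the PP analysis".
- **ITT:** "All correctly included patients will be included in the ITT analysis set". Its role is to confirm the PP result, and the text limits that role: "confirmed by an analysis of the ITT analysis set (only for the primary objective").
- **Safety set:** "demography and treatment safety related conclusions will be based on the results from the safety analysis set".

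The secondary outcomes are in Table 1 (Section 2.2) and Table 6 (Section 6.2): NBD score at 6, 9 and 12 months, EQ-5D-3L, product compliance, satisfaction, urinary tract infection and health-economic variables. Compliance appears in Table 6 as "To investigate study product compliance" and is measured by "PRO variables (“Do you still perform TAI with Navina Smart?” Yes/No"). It is to be described at 3 and 12 months. Neither table names an analysis set.

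Section 4.5.1 lists among the grounds for discontinuation "Severe non-compliance to protocol as judged by the investigator and/or WHC". It also refers the reader to Section 7.2 for how discontinued subjects' data are handled. Section 7.2 does not mention them. Section 7.1.3 rules out imputation.

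**The concern.** The primary endpoint has an ITT check. The later NBD scores do not, because the protocol expressly confines ITT to the primary objective. This is a stated rule rather than a detail left open, and an analysis plan that follows the protocol would inherit it. In a single-arm before-after study no comparator offsets selection. If subjects with poor results leave or deviate and so fall outside PP, the 12-month change describes those for whom the system worked well enough to continue. EQ-5D-3L changes also feed the QALY calculations (Section 6.4.2).

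Compliance raises a further problem. Sections 3.1 and 3.3 make compliance and the reasons for non-compliance secondary objectives, and 3.3 names poor compliance over time as an evidence gap. A compliance rate computed in a set chosen partly for adherence is conditioned on what it measures. The protocol does not say that this will be done, but nothing in it prevents it. The one cross-reference that should settle the treatment of discontinued subjects leads to a section that does not address it.

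**Working it through.** **Step 1. Which set each outcome has under Section 7.2**

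| Outcome | Set |
|---|---|
| NBD score, 3 months (primary) | PP, confirmed in ITT |
| NBD score, 6, 9 and 12 months | PP only |
| EQ-5D-3L | PP only if it counts as efficacy; otherwise none named |
| Compliance, satisfaction, urinary tract infection | none named |
| Demography, adverse events | safety set |

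**Step 2. The plan's own figures (Section 7.4)**

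Inputs: Z values 1.96 and 1.28, SD of the difference 2.2, difference 0.8.

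N = (1.96 + 1.28)² × 2.2² / 0.8² = 10.4976 × 4.84 / 0.64 = 79.39, rounded up to 80.

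Drop-out allowance: 150 − 80 = 70, and 70/150 = 46.7%. The stated 80, 150 and 47% are reproduced. Whether an SD of 2.2 is right is a separate matter and does not affect this point.

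**Step 3. What a PP denominator could do to compliance**

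Assumptions: all 70 tolerated drop-outs stopped irrigating and would answer No, and the other 80 would answer Yes. Let f be the share of stoppers whom the PP definition excludes. The documents give no value for f, so a range is shown.

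PP compliance = 80 / (80 + 70 × (1 − f))

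| f | PP size | Compliance in PP |
|---|---|---|
| 0 | 150 | 80/150 = 53.3% |
| 0.5 | 115 | 80/115 = 69.6% |
| 0.75 | 97.5 | 80/97.5 = 82.1% |
| 0.9 | 87 | 80/87 = 92.0% |
| 1 | 80 | 80/80 = 100% |

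In all 150 subjects the figure is 53.3% whatever f is. At f = 0.5 the overstatement is 69.6 − 53.3 = 16.3 percentage points. To exceed 90%, 70 × (1 − f) must be below 80/0.9 − 80 = 8.9, so f must be above 0.873.

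**Step 4. Other discontinuation rates**

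Section 7.4 also cites rates of 45% and 55% from earlier studies of irrigation. Applied to 150 subjects:

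- At 45%: 82.5 continue, so 55.0% in all subjects. In PP, 71.0% at f = 0.5 and 83.0% at f = 0.75.
- At 55%: 67.5 continue, so 45.0% in all subjects. In PP, 62.1% at f = 0.5 and 76.6% at f = 0.75.

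No comparable figure can be computed for the NBD score or EQ-5D-3L, because the documents say nothing about how outcomes differ between subjects inside and outside PP.

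**The case against.** A reader might infer that, with ITT confined to the primary objective and the safety set reserved for other uses, every secondary outcome falls to PP by elimination, and that reported compliance must then be near 100% by construction. The documents do not support this, for four reasons.

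- Section 7.2 ties PP to efficacy conclusions. Sections 3.1 and 3.3 list compliance and satisfaction apart from efficacy (3.3 also lists quality of life apart from it), and the tables name no set. Naming one for a descriptive outcome is often left to the analysis plan.
- PP does not expressly exclude subjects who stop irrigating. That turns on the undefined major deviations, and Section 4.5.1 lists voluntary discontinuation separately from severe non-compliance.
- The protocol plans to collect data from those who leave. NBD score, EQ-5D-3L and the Follow-up Questionnaire are also completed at early withdrawal (Sections 6.4.1, 6.4.2, 6.4.4), and Section 4.5.2 requires asking why a subject stopped. It would be wrong to say that compliance cannot be estimated.
- The 70 of 150 is a tolerated loss in a 3-month sample-size calculation, not a forecast of persistence, and leaving the study is not the same as stopping irrigation.

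All four stand, and they limit the compliance point to a risk. They do not touch the restriction of ITT to the primary objective, which is explicit, or the cross-reference from 4.5.1 that 7.2 leaves unanswered.

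**Conclusion.** The point holds in two parts of different strength.

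**Firm:** as written, conclusions on the NBD score at 6, 9 and 12 months rest on PP alone, and so do those on EQ-5D-3L if it is treated as efficacy. The study has no control arm, no imputation and an allowance of 47% drop-out. Selection towards continuing subjects is to be expected; its size cannot be derived from the documents.

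**Conditional:** compliance and satisfaction have no assigned set, and the handling of discontinued subjects' data is promised but not given. If compliance were reported in PP, the result could be anything from 53% to 100% where the all-subject figure is 53%, depending on an exclusion share that the documents do not state. The 100% end needs every stopper to be excluded, so it is the extreme of the range and not a consequence of the text.

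The primary analysis keeps its ITT confirmation and is not affected. The change should be made, but it does not threaten the main result.

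**What to change.** In Section 7.2:

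1. Delete the bracketed limit of the ITT analysis to the primary objective.
2. Analyse the NBD score at 6, 9 and 12 months, EQ-5D-3L and satisfaction in the ITT set, including the questionnaires completed at early withdrawal, with PP as supportive. Say at which time point an early-withdrawal questionnaire is counted. Without imputation, ITT will still lack subjects who returned nothing, so show the number contributing at each time point.
3. Report product compliance and reasons for non-compliance on all treated subjects. Count subjects known to have stopped irrigation as No. Show those with unknown status separately, with a sensitivity range from all No to all Yes. Counting every lost subject as No in the main table would be an imputation at odds with Section 7.1.3, so it belongs only in that range.
4. State how discontinued subjects' data are used, so that the reference from Section 4.5.1 is answered.

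The cost is protocol and analysis-plan wording and a few extra tables. The questionnaires are already planned, so no new data collection is needed. The reported figures will probably be less favourable.
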